#### **11.8.2.5. Safety Analysis**

---

MedDRA will be used for the medical coding of adverse events and serious adverse events, classified and counted according to the SOC and PT. The solicited adverse events for the reactogenic subgroup will be classified and counted according to the inoculation site and non-inoculation site (systemic) adverse events specified in the protocol. TEAE will be mainly analyzed in this study and the adverse events that occurred before vaccination will be listed in the form of a list. Unless otherwise specified, the following adverse events are TEAEs.

The frequency, number, and incidence of all adverse events and AESIs, adverse events and AESIs related to the study vaccine, adverse events and AESIs unrelated to the study vaccine, adverse events and AESIs of grade 3 or above, and adverse events and AESIs of grade 3 or above related to the study vaccine will be calculated respectively in the test group and control group. Fisher's precision probability test will be used to compare the differences between groups in the incidence of the above adverse events. The occurrence time and severity of adverse events will be statistically described. The adverse events and AESIs related to the study vaccine or unrelated to the study vaccine will be listed respectively.

The frequency, number, and incidence of all serious adverse events, serious adverse events related to the study vaccine, and serious adverse events not related to the study vaccine will be calculated respectively in the test group and control group. Fisher's precision probability test will be used to compare the differences between groups in the incidence of the above adverse events. The serious adverse events will be listed.

#### **11.8.3. Interim Analysis**

Not applicable.

#### **11.8.4. Handling of missing data**

In the statistical analysis of I-FAS, the last observation carried forward (LOCF) method will be used to carry forward the missing data of antibody results after vaccination, and derive the corresponding immunogenicity endpoints. Missing data in the safety evaluation endpoint and immune persistence endpoint will not be processed

---

in this study. Details on the treatment of missing data are provided in the Statistical Analysis Plan.

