## **11.8. Statistical analysis**

### **11.8.1. Analysis Sets**

#### **➤ Analysis set of efficacy**

**Full analysis set of efficacy(E-FAS):** Include all subjects who followed the intention-to-treat (ITT) principle, entered randomization and completed vaccination, and had at least one case surveillance follow-up after vaccination.

**Modified full analysis set of efficacy(E-mFAS):** It is a subset of E-FAS and includes all subjects who completed vaccination, had negative baseline nucleic acid results, and had at least 1 case surveillance follow-up 14 days after vaccination. Among them, COVID-19 cases with positive nucleic acid or antigen test or confirmed diagnosis within 14 days from enrollment to vaccination will also be excluded from this analysis set.

**Per protocol set of efficacy(E-PPS):** It is a subset of E-mFAS, including all subjects who did not violate the inclusion/exclusion criteria, completed vaccination, had negative baseline nucleic acid results, and had at least one case surveillance follow-up 14 days after vaccination, and did not violate the protocol. Among them, COVID-19 cases with positive nucleic acid or antigen test or confirmed diagnosis within 14 days from enrollment to vaccination will also be excluded from this analysis set.

Cases of E-mFAS and E-PPS are counted from 14 days after vaccination and are

---

mainly used for the evaluation of the main protective efficacy of the vaccine. Among them, E-mFAS is the main analysis set for the evaluation of protective efficacy in this study. E-FAS was used to evaluate the protective efficacy after vaccination.

➤ **Analysis set of immunogenicity**

**Full analysis set of immunogenicity(I-FAS):** Include all subjects in the immunization subgroup who follow the ITT principle, enter randomization and complete vaccination, and have valid antibody data before vaccination.

**Per protocol set of immunogenicity(I-PPS):** Include all subjects in the immunization subgroup who did not violate the inclusion/exclusion criteria, completed the vaccination, had blood samples collected at the evaluation time points, and had valid antibody data. The immunogenicity analysis sets were defined for the immunogenicity evaluation of each group at 7 days, 14 days, and 28 days after vaccination respectively.

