**Analysis set of immune persistence(IPS):** Include subjects whose blood samples were collected at all immune persistence evaluation time points and have valid antibody data. The immune persistence analysis set was defined for the immunogenicity evaluation at 3 and 6 months post-vaccination, respectively.

I-FAS and I-PPS were used for immunogenicity analysis. IPS was used for immune persistence analysis.

➤ **Analysis set of safety**

**Safety analysis set(SS):** Include all subjects vaccinated with the study vaccine.

All the above analysis sets will be discussed and decided by the main investigators, funders, statisticians, and data managers in a blinded data review meeting before the database is locked.

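### LOCF in the immunogenicity full analysis set can carry baseline or early titres into days 7 to 28, most likely understating the vaccine response

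*Protocol*

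**What the plan says.** Three parts of the protocol bear on this.

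- **The filling rule (section 11.8.4).** In I-FAS, "the last observation carried forward (LOCF) method will be used to carry forward the missing data of antibody results after vaccination", and the filled data are then used to "derive the corresponding immunogenicity endpoints". The same paragraph limits the rule: "Missing data in the safety evaluation endpoint and immune persistence endpoint will not be processed". It closes with a referral: "Details on the treatment of missing data are provided in the Statistical Analysis Plan".
- **Who is in I-FAS (section 11.8.1).** Participants in the immunogenicity subgroup who "enter randomization and complete vaccination, and have valid antibody data before vaccination". No post-vaccination sample is required. The per-protocol set (I-PPS) differs: its members "did not violate the inclusion/exclusion criteria, completed the vaccination, had blood samples collected at the evaluation time points, and had valid antibody data", and it is defined separately for days 7, 14 and 28.
- **How the sets are used (section 11.8.1).** "I-FAS and I-PPS were used for immunogenicity analysis. IPS was used for immune persistence analysis". Neither I-FAS nor I-PPS is named as the main one.

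Section 6.5.2 puts 50 participants per arm in the subgroup, sampled before vaccination and at 7, 14 and 28 days, 3 months and 6 months. Section 6.2.2 makes GMT, GMI and seroconversion at these times secondary endpoints.

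**The concern.** After a booster, titres are expected to climb between day 0 and day 28. LOCF assumes that a titre stays where it was last seen, which is least plausible over exactly these visits. On placebo, where titres should stay roughly flat, a carried value does little harm. On vaccine it replaces a response with something close to no response. The error therefore differs between arms and shrinks the vaccine-placebo difference.

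The entry condition for I-FAS makes this worse. A participant with no post-vaccination sample still belongs to the set, and the only titre available to carry is the baseline one. At stake is a secondary immunogenicity result in one of the two sets on which it will be reported.

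**Working it through.** The protocol gives no titre effect, no standard deviation and no missing rate for the subgroup, so there is no planned figure to reproduce. The check is what the rule does by missing pattern, followed by its size under stated assumptions.

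**1. What is carried**

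| Missing sample(s) | Value available to carry |
|---|---|
| Day 7 only | Baseline |
| Days 7, 14 and 28 | Baseline at all three visits |
| Day 14 only | Day 7 |
| Day 28 only | Day 14 |

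**2. Consequence for seroconversion**

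The synopsis definition requires a post-vaccination neutralizing titre of at least 4 times baseline, or at least 4 times the detection limit if baseline was below it. A carried baseline has a fold-rise of 1, so the participant is always counted as a non-seroconverter.

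**3. Size for the GMT ratio**

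Assumptions: true vaccine-to-placebo ratio F = 10, placebo flat, equal baseline GMT, share m missing in each arm, and missingness unrelated to titre.

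- Baseline carried: ratio = F^(1 − m).
- Day 7 carried, having reached share s of the log rise: ratio = F^(1 − m(1 − s)), with s = 0.5 assumed.

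| m | Baseline carried | Day 7 carried, s = 0.5 | 90% seroconversion reads, baseline carried |
|---|---|---|---|
| 5% | 10^0.95 = 8.9 | 10^0.975 = 9.4 | 0.90 × 0.95 = 85.5% |
| 10% | 10^0.90 = 7.9 | 10^0.95 = 8.9 | 0.90 × 0.90 = 81% |
| 20% | 10^0.80 = 6.3 | 10^0.90 = 7.9 | 0.90 × 0.80 = 72% |

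At 10% missing (5 of 50 per arm), the GMT ratio is understated by about 21% with baseline carried (1 − 0.794) and about 11% with day 7 carried (1 − 0.891).

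**4. Sensitivity to the assumptions**

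- With baseline carried for 10%, a true ratio of 5 reads 4.3 and a true ratio of 20 reads 14.8.
- With day 7 carried for 10% and F = 10, the ratio reads 8.5 if s = 0.3 and 9.5 to 9.6 if s = 0.8.

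**The case against.** **Carrying baseline is an inference, and details go to the SAP.** Both are true. Section 11.8.4 neither states nor forbids carrying a pre-vaccination titre. However, the method and the set are fixed in the protocol, and only details are deferred. Filling a missed day 7 in this set leaves no other value to use. Even if the SAP ruled out baseline, an early titre would still be carried along a rising curve.

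**An observed-sample analysis already exists.** I-PPS uses collected samples at each of days 7, 14 and 28, and the persistence endpoints are not imputed. This stands and limits the damage. It does not make the I-FAS result sound, because I-FAS is reported beside I-PPS and neither takes precedence.

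**The larger figures are a worst case.** This also stands. A participant who misses only day 28 carries day 14, not baseline, so the day-7 column is the fairer guide for many patterns. The 20% non-evaluable allowance in section 6.5.1 concerns efficacy sizing and is not a missing rate for this subgroup.

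**Two stronger readings are tempting, and the documents do not support them.**

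- A reader might infer that titres drawn after a SARS-CoV-2 infection are deliberately kept and so bias the comparison, since section 11.8.1 removes early cases from two efficacy sets but says nothing similar for the immunogenicity sets. Silence is not a rule to keep them. The sets are settled at a blinded data review, and the SAP may address the matter. Excluding such titres would also condition on an event after randomization.
- A reader might infer that LOCF makes the intervals too narrow because filled values count as observed. In this illustration the opposite happens. Mixing 10% baseline values into a 10-fold rise adds 0.1 × 0.9 × 1² = 0.09 to the log10 variance. With an assumed SD of 0.5 log10, the standard error is √(0.34/50) = 0.082, against 0.5/√45 = 0.075 on observed data. The filled interval is wider whenever (SD² + 0.09)/50 exceeds SD²/45, that is, for any SD below 0.9 log10. For seroconversion the standard errors are √(0.81 × 0.19/50) = 5.5 points against √(0.90 × 0.10/45) = 4.5 points.

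**Conclusion.** The point holds for I-FAS at days 7, 14 and 28. The protocol fixes a single-imputation rule that suits a stable measurement and applies it to one expected to rise, in a set whose entry condition lets the rule reach back to baseline. The most likely result is an understated vaccine response and a smaller vaccine-placebo difference. Under the stated assumptions at 10% missing, a GMT ratio of 10 reads between 7.9 and 8.9, and a 90% seroconversion rate reads 81% in the baseline case.

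The direction depends on titres rising at the missed visit; had they passed their peak, LOCF would overstate them. The size rests entirely on assumed values for the rise, the missing share and the day-7 level. The primary vaccine efficacy analysis is untouched. This is a weakness in secondary endpoints measured in 100 participants, and it is worth correcting because the correction is cheap.

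**What to change.** In section 11.8.4, replace LOCF for I-FAS with a mixed model for repeated measures on log titre, with group, visit, group-by-visit interaction and log baseline titre, fitted to all observed values. Report seroconversion on observed samples, with the number contributing at each visit. LOCF may stay as a sensitivity analysis. Section 11.8.2.4, which names a t-test on log titres, should be brought into line for this set.

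The cost is a change of protocol wording and slightly more analysis work; no new data are needed. The model relies on a missing-at-random assumption, which should be stated. Participants with no post-vaccination sample would contribute no response value, instead of being counted as having had no response.

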#### **11.8.5. Multiplicity Analysis**

Not applicable.

### **12. Subject Safety and adverse event management**

#### **12.1. Adverse Event Definition**

Adverse Event (AE): it refers to all adverse medical events that occur after participants receive the vaccine/drug for the study, which can be manifested as symptoms, signs, diseases, or laboratory test abnormalities, but are not necessarily related to the study vaccine/drug.

Adverse Vaccine Reaction (AVR): it refers to any harmful or unexpected reactions that may occur in clinical trials and be related to the study vaccine. There is at least a reasonable possibility of a causal relationship between the study vaccine and the AE, i.e., the correlation cannot be ruled out.

Serious Adverse Event (SAE): it refers to the adverse medical event that causes death, is life-threatening, leads to permanent or serious disability or incapability, requires hospitalization or prolonged hospitalization, and results in congenital abnormalities or birth defects after the participants receive the study drug/vaccine.

Advent Events of Special Interesting (AESI): refers to the adverse event of special scientific and medical interest to a product or project, which may or may not be a serious event. The investigator should be able to monitor them on an ongoing basis and report them promptly to the sponsor. For applicable AE, the investigator should investigate further to describe and understand them. Depending on the nature of the event, the sponsor may also need to communicate and/or report it to other interested parties.

Suspected Unexpected Serious Adverse Reaction (SUSAR): it refers to suspected unexpected serious adverse reactions whose clinical manifestations are beyond the

---

Investigator's Brochure for the study drug/vaccine, package inserts for marketed drugs/vaccines, summary of product characteristics, and other existing information in terms of their nature and severity.

Adverse Events Following Immunization (AEFI): It refers to the reaction or event suspected to be related to vaccination after vaccination.

## **12.2. Security precaution**

The first-aid facilities and equipment in the first-aid room are effective, the first-aid drugs are within the validity period, and the first-aid doctors have corresponding qualifications and capabilities. When the participant has an adverse event at the study site, he/she will be treated in the on-site emergency room on time, and follow-up hospitalization will be arranged according to the arrangement. During the enrollment of the participants, the agreement department shall be notified to prepare for timely treatment. A strict SOP is required to specify the responsibilities of the investigator, the contact telephone number of the investigator, the route of the ambulance, etc. to ensure that the unexpected adverse events can be dealt with on time. When the participant needs to be hospitalized for emergency treatment after serious adverse events, the agreed department can provide green channel services such as medical treatment, hospitalization, and medical security to ensure that the participant can be treated in time.

The sponsor shall designate full-time personnel to be responsible for the safety information monitoring and SAE reporting management of the clinical study. Both the sponsor and the investigator should develop standard operating procedures for safety information monitoring and SAE reporting in the clinical study, and train all relevant personnel. The monitoring and reporting of adverse events in vaccine clinical study shall be completed jointly by participants, adverse event investigators, and investigators at different observation time points in stages.

---

### **12.3. Discovery and Collection of Adverse Events**

During the training of participants, it should be emphasized that adverse events need to be reported promptly, and investigators should be highly alert to such events and investigate and handle them promptly.

For solicited AEs and unsolicited AEs, ask the participants if they have received hospitalization and outpatient treatment or taken drugs, and record this information.

When a serious adverse event occurs, the investigator is responsible for reviewing all documents related to the event (e.g.: hospital course, medical order records, laboratory reports, and diagnostic reports), or to clarify the nature and relevance of SAEs, the investigator arranges clinical examinations/tests as required. If a participant is confirmed dead during study participation or the follow-up period, the hospital's conclusion on the deceased person should be collected, and a copy of the results, including histopathology results, should be obtained if an autopsy is performed.

The investigator should try to collect complete copies of medical records, but cannot replace study records with copies of medical records of participants. All information related to serious adverse events should be recorded on the original records and serious adverse event report pages.

If medical records are to be released for medical evaluation purposes, all fields identifying the participant should be masked before release.

### **12.4. Treatment and Management of Adverse Events**

If AE occurs in the participants in the study, the investigator and specialist should closely monitor the changes of AE in the participants and give corresponding treatment if necessary.

---

The investigator should establish an emergency plan for SAE handling in the clinical study, train all relevant personnel, and take measures to know any clinically significant disease/event after the vaccination of subjects. By the relevant national regulations and current medical management practices, the participants will be promptly sent to the designated hospital for appropriate treatment. Medications used to treat AEs should be recorded in the participant's source records and EDC.

In case of disagreement and dispute in the handling of adverse events, the investigator shall be obliged to cooperate with the sponsor in handling and assisting the participants in medical identification.

The sponsor has the obligation and responsibility to guarantee the safety of the participants unconditionally. For the confirmed adverse reactions related to the vaccine, the sponsor shall compensate the participants under the requirements of the Vaccine Administration Law of the People's Republic of China, the Regulations on the Administration of Vaccine Circulation and Vaccination, and the Measures for Compensation of Abnormal Reactions to Vaccination (Trial) of each province.

The investigator should pay continuous attention to the adverse events that persist due to study termination or the end of the visit. The adverse events related to vaccination should be followed up until the end of the event. The follow-up can be stopped after the unrelated events are diagnosed by the doctor.

## **12.5. Serious Adverse Event Reporting**

### **12.5.1. Reporting Procedure**

Investigators should fill out the initial report of the Serious Adverse Event Report

---

Form within 24 hours after learning SAE and report it to the sponsor and CRO on behalf of the sponsor by e-mail. After the initial report, the investigator should continue to follow up the SAE and report new information or changes to the previous report, event outcomes, etc. in the form of follow-up/summary reports, to pay attention to the serious adverse events that have not recovered/have not recovered or are recovering/are recovering until recovery/condition is stable, and complete the summary report. If the participant is diagnosed with COVID-19 and meets SAE standards, they may not report SAE; If at this point, the combined underlying disease worsens and meets SAE standards, then the exacerbation of the underlying disease needs to be reported as SAE. For reports involving fatalities, the investigator should provide the sponsor and the IRB/EC or other parties as required with any additional information requested, such as autopsy reports and final medical reports.

#### Start/end dates of AE/SAE

(1) AE/SAE start date: for a new disease, the date of appearance of first relevant signs/symptoms is defined as the AE/SAE start date; for previous diseases (defined as the medical history before enrollment and still present at vaccination), the date of first exacerbation of signs/symptoms is used as the AE/SAE start date, not the date of participant reporting or investigator learning of them; if the AE/SAE is an abnormal laboratory test after vaccination with clinical significance, the start date is recorded as the sampling date.

AE/SAE end date: for a new disease, the last day that the relevant signs/symptoms lasted is defined as the AE/SAE end date; for the AE/SAE or abnormal laboratory test value caused by exacerbation of previous diseases, the date when the signs and symptoms return to the baseline level or the state is better than the baseline level, and the investigator evaluates that the event has been stable, is defined as the AE/SAE end date; if the AE/SAE is an abnormal laboratory test after vaccination with clinical significance, the end date is the sampling date that the result return to normal.

It should be noted that the start/end date of SAE resulting in

---

hospitalization/prolongation of hospitalization is also based on the above judgment rules, with the date of appearance of first relevant signs/symptoms as the start date of SAE, rather than the date of hospitalization/prolongation of hospitalization (unless the date of hospitalization/prolongation of hospitalization is the same as the date of appearance of first relevant signs/symptoms); the last day that the relevant signs/symptoms lasted is defined as the SAE end date, rather than the discharge date (unless the discharge date is the same as the last day of relevant signs/symptoms presence); The end date of SAE resulting in death is defined as the date of death. When recording AEs in the eCRF, use accepted medical terminology whenever possible. To improve the quality and accuracy of AE information collection, the investigator should follow the following guidelines.

- AE records are recorded in eCRF using accepted medical terminology whenever possible. Record and report SAEs.
- Document the diagnosis (i.e., the disease or syndrome) rather than the associated signs, symptoms, and laboratory findings (e.g., document congestive heart failure rather than dyspnea, rales, and cyanosis).
- Document and report SAEs that result in death.
- For patients hospitalized for a surgical or diagnostic procedure, the disease that led to the surgical or diagnostic procedure should be documented as an SAE, not the procedure itself. The process should be documented in the measures for disease treatment section of the case narrative.
- Pregnancies that occur in participants during the study period are not considered AEs per se but should be recorded on a separate pregnancy record form, and the pregnancy report should be sent to the sponsor and the sponsor's designated CRO within 24 hours. If the outcome of the pregnancy meets SAE criteria (including spontaneous abortion, stillbirth, or any congenital anomalies, etc.), the investigator should report it according to the SAE reporting process.

The investigator should sign off and read the relevant safety information provided by the sponsor for the clinical study promptly and consider the participant's treatment,

---

whether to adjust it accordingly, communicate with the participant as early as possible if necessary, and report suspected and unintended SAE provided by the sponsor to the IRB/EC or other parties if needed.

After being informed of the SAE report, the sponsor is required to conduct a comprehensive analysis and evaluation of the SAE as soon as possible; the initial report is required to be submitted to all investigators participating in the clinical study, the clinical study institution, the IRB/EC, the drug regulatory authority, and the health care authority in accordance according to the following timelines:

- (1) For SUSAR that are fatal or life-threatening, the sponsor shall report them as soon as possible after the initial notification, but not later than 7 calendar days, and report the relevant follow-up information within the following 8 calendar days.
- (2) For SUSAR that are not fatal or life-threatening, the sponsor shall report them as soon as possible after first becoming aware of them, but no later than 15 calendar days.
- (3) For other potentially serious safety risk information, the sponsor shall report it as soon as possible after first becoming aware of it, but no later than 15 calendar days.

The Sponsor has a duty and responsibility to ensure the safety of participants, to provide humane care to participants who experience AE during participation in clinical studies, and to treat and compensate participants whose AE is determined to be related to vaccination.

